#### Assessment of carotid intima-media thickness

Carotid ultrasonography to assess IMT was performed by two investigators specifically trained for this before starting the study. A Sonosite Micromax ultrasound (Sonosite Inc., Bothell, Washington, USA) device paired with a 5-10 Mhz multifrequency high-resolution linear transducer with Sonocal software was used for performing automatic measurements of IMT for optimising reproducibility. Measurements were made of the primitive carotid after the examination of a longitudinal section of 10 mm at a distance of 1 cm from the bifurcation, performing measurements in the anterior or proximal wall, and in the posterior or distal wall in the lateral, anterior and posterior projections, following an axis perpendicular to the artery to discriminate two lines, one for the intima-blood interface and the other to the media-adventitious interface. A total of 6 measurements were obtained of the right carotid and other 6 of the left carotid, using average values (average IMT) and maximum values (maximum IMT) calculated by the software automatically. The measurements were obtained with the subject lying down, with the head extended and slightly turned opposite to the carotid examined, following the recommendations of the Manheim Carotid Intima-Media Thickness Consensus [38]. Finally, IMT image is frozen in telediastole by means of electrocardiogram triggering to avoid a confounding effect of pulsatile deformation of wall thickness and transferred to a computer. The average IMT was considered to be abnormal if it was above 0.9 mm, or if there were atherosclerotic plaques with a diameter over 1.5 mm, or a focal increase of 0.5 mm, or 50% of the adjacent IMT [16].

#### Evaluation of peripheral artery involvement

This was evaluated using the ankle-brachial index (ABI), performed in the morning without having consumed coffee or tobacco for at least 8 hours prior to measuring and an ambient temperature of 22-24°C. With the feet uncovered, in a supine decubitus position after 20 minutes of rest, the pressure in the lower extremities was measured using a portable Doppler system Minidop Es-100Vx (Hadeco, Inc. Arima, Miyamae-ku, Kawasaki, Japan) applying the probe at the anterior or posterior tibial artery at an angle of approximately 60° to the direction of blood flow. The transducer's cuff was quickly inflated in each ankle about 30 mmHg above the systolic pressure and the pressure was allowed to descend (by about 2 mmHg per second) until the first sound corresponding to the systolic pressure was heard. The blood pressure was also measured in both arms (measured twice at 3-5 minute intervals). The ABI was calculated separately for each foot by dividing the higher of the two systolic pressures in the ankle by the highest of the two systolic pressures in the arm [39]. It is considered subclinical organ damage if it is lower than 0.9 [16].

#### Cardiac assessment

The electrocardiographic examination was performed with a General Electric MAC 3.500 ECG System (Niskayuna, New York, USA), that measures automatically the voltage and duration of waves and estimates the criteria of the Cornell voltage-duration product (Cornell VDP) [40] to assess the LVH by the following equation: Men ((RaVL + SV3) * QRS) and women ((RaVL + SV3) * QRS + 6). LVH is defined as the voltage-duration product > 2,440 mm/ms (16). We will estimate left ventricular mass index (LVMI) by Novacode equation [41].

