#### Renal assessment

The kidney damage was assessed by measuring creatinine plasma concentration, the glomerular filtration rate was estimated by CKD-EPI (Chronic Kidney Disease Epidemiology Collaboration) [42] and the MDRD-IDMS (Modification of Diet in Renal Disease-Isotopic Dilution Mass Spectrometry) [43] equation and proteinuria were assessed by the albumin/creatinine ratio following the 2007 European Society of Hypertension/European Society of Cardiology Guidelines criteria [16]. Subclinical organ damage was defined as plasma creatinine between 1.3 - 1.5 mg/dl in men and 1.2 - 1.4 mg/dl in women, glomerular filtration rate below 60 ml/min or albumin/creatinine ratio > 22 mg/gr in men and 31 mg/gr in women. Renal disease was defined as plasma creatinine of 1.5 mg/dl or higher in men and 1.4 mg/l in women or albumin/creatinine ratio > 300 mg/24 h.

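### As printed, the women's Cornell formula makes the sex correction negligible, and the renal-disease limits carry a creatinine unit and a ratio unit that do not fit; the definitions need correcting and the LVH derivation needs checking

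*Protocol article*

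**What the plan says.** **Protocol article, Cardiac assessment.** The Cornell voltage-duration product is given as "Men ((RaVL + SV3) * QRS) and women ((RaVL + SV3) * QRS + 6". One cut-off serves both sexes: "LVH is defined as the voltage-duration product > 2,440 mm/ms". The section also says that the ECG system "measures automatically the voltage and duration of waves and estimates the criteria of the Cornell voltage-duration product". Left ventricular mass index by the Novacode equation is planned as a further cardiac measure.

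**Protocol article, Renal assessment.** Subclinical damage includes "plasma creatinine between 1.3 - 1.5 mg/dl in men and 1.2 - 1.4 mg/dl in women", or "albumin/creatinine ratio > 22 mg/gr in men and 31 mg/gr in women", or a glomerular filtration rate below 60 ml/min. The more severe class reads "Renal disease was defined as plasma creatinine of 1.5 mg/dl or higher in men and 1.4 mg/l in women". A second criterion, sufficient on its own for that class, is "albumin/creatinine ratio > 300 mg/24 h".

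**Where these outcomes are used.** The objectives name LVH and renal damage among the outcomes. The sample-size paragraph under Study subjects counts newly arising target organ damage as an event. Statistics analysis compares time to event by log-rank test and Cox regression.

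**The concern.** A separate formula for women is pointless unless it changes the classification, and the printed one hardly does. The 6 can be added to a voltage in mm but not to a product in mm × ms, so the units also show that the bracket is misplaced. The cut-off is printed in mm/ms, a quotient unit, although the quantity is a product.

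The renal definitions have a similar fault. The women's limit for the severe class is in a different unit from every other creatinine limit in the section and, taken literally, falls below the milder class. The ratio is in mg per gram for one class and in a 24-hour excretion unit for the other.

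These are thresholds inside outcome definitions. If code were written from the article, LVH in women would be missed at baseline and at follow-up, an error in one sex only. The renal classes for women could not be assigned coherently. With 110 patients planned, a small number of misassigned patients could matter to the event analysis.

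**Working it through.** The plan states no result to reproduce here, so the check is of formulas and units.

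**Inputs.** The two Cornell formulas and the 2,440 cut-off come from Cardiac assessment; the creatinine and ratio limits come from Renal assessment. QRS duration is not given in the document. I assume 80–120 ms and show the range.

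**1. Size of the printed sex correction.** 6 / 2,440 = 0.25% of the cut-off.

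**2. Voltage (RaVL + SV3) needed to exceed 2,440.**
- Men: 2,440 / QRS
- Women as printed: (2,440 − 6) / QRS
- Women with the 6 inside the bracket: 2,440 / QRS − 6

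| QRS (ms, assumed) | Men (mm) | Women, as printed (mm) | Women, 6 inside (mm) | Printed minus inside (mm) | Relative excess |
|---|---|---|---|---|---|
| 80 | 30.50 | 30.43 | 24.50 | 5.93 | 24% |
| 90 | 27.11 | 27.04 | 21.11 | 5.93 | 28% |
| 100 | 24.40 | 24.34 | 18.40 | 5.94 | 32% |
| 110 | 22.18 | 22.13 | 16.18 | 5.95 | 37% |
| 120 | 20.33 | 20.28 | 14.33 | 5.95 | 42% |

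The last column is the printed threshold divided by the inside threshold, minus 1; for example, 24.34 / 18.40 − 1 = 32%. As printed, the sexes differ by 6 / QRS, which is 0.05–0.075 mm over this range.

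**3. One patient.** Take a woman with 20 mm at QRS 100 ms. As printed: 20 × 100 + 6 = 2,006, LVH-negative. With the 6 inside: (20 + 6) × 100 = 2,600, LVH-positive. At 100 ms the two rules disagree for women above 18.40 mm and up to 24.34 mm.

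**4. Women's creatinine.** 1.4 mg/l ÷ 10 = 0.14 mg/dl. The lower end of the women's subclinical band is 1.2 mg/dl, and 1.2 / 0.14 = 8.6. The severe limit is therefore about one ninth of the start of the milder band, and every woman in that band would also meet the severe definition. In mg/dl, the limit meets the top of the band at 1.4.

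**5. Ratio.** Subclinical limits are in mg/g. The severe limit of 300 is in mg/24 h, which is an excretion over time. A ratio cannot be compared with it, so the criterion cannot be applied as written.

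**6. Class boundaries.** Reading the bands as including their ends, a man at exactly 1.5 mg/dl is in both classes. Once the unit is corrected, so is a woman at exactly 1.4 mg/dl.

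**The case against.** The strongest reply is that the printed equation may never have been used. The article says that the ECG system estimates the Cornell criterion automatically, so the equation may only describe what the device does, and a bracket misplaced in print does not alter device output. This stands. A reader might infer that LVH in women is under-detected in the trial's data. The document does not support that; the effect is conditional on the printed formula being used. The Novacode mass index is untouched in any case.

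Second, the mg/l looks like a slip that a reader can resolve, because the men's limit in the same sentence and both subclinical bands are in mg/dl. This also stands. A reader might infer that the rule leaves no woman at risk of new renal disease. That requires someone to apply 0.14 mg/dl, and nothing suggests this. The women's limits for filtration rate and for the subclinical ratio are in coherent units. The event definition does not say that the severe renal class enters it.

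Third, a reader might conclude that the 300 limit misclassifies patients, or that it must be 300 mg/g. Neither follows. The limit is inapplicable rather than wrong by a known amount, and either the unit or the named quantity could be at fault. The cited guideline is not at hand to decide.

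Fourth, the overlap at a single creatinine value is minor, since such a patient has renal damage under either class. That is fair. None of these replies makes the printed definitions correct.

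**Conclusion.** The definitions are wrong as printed and should be corrected; no effect on trial data is shown.

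- **Cornell formula.** The sex correction is negligible at 0.25% of the cut-off, and mm/ms is the wrong unit for a product. If LVH is derived from this line, the women's voltage threshold is about 6 mm too high relative to the bracketed form. That is 28–32% at an assumed QRS of 90–100 ms and 24–42% over 80–120 ms. LVH would then be under-detected in women only. The placement of the 6 inside the bracket is inferred from units and magnitude, as the source formula is not reproduced in the article.
- **Renal limits.** The women's creatinine limit contradicts the section's own subclinical band, and the intended unit can be read from the same section. The 300 limit does not fit the quantity it is attached to, and the document does not settle which of the two to change. The classes touch at 1.5 mg/dl in men and, once the unit is corrected, at 1.4 mg/dl in women.

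This is more than cosmetic, because LVH and renal damage are named outcomes and new organ damage counts as an event.

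**What to change.** 1. Write the women's formula as (RaVL + SV3 + 6) × QRS and give the 2,440 cut-off in mm × ms.
2. Confirm which formula the ECG device or the analysis code uses. If it is the printed one, recompute LVH in women from the stored voltages and QRS durations at all visits.
3. State the women's renal-disease creatinine limit in mg/dl, consistent with the rest of the section.
4. Reconcile the 300 limit with the cited guideline so that the quantity and the unit match.
5. State which class a value on the boundary belongs to, so that subclinical damage and renal disease do not overlap in either sex.

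The cost is a few corrected lines and one check of the device settings or code. Recomputation is needed only if that check fails, and it needs no new patient measurements if the voltages and durations were stored.

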#### Renal assessment

The kidney damage was assessed by measuring creatinine plasma concentration, the glomerular filtration rate was estimated by CKD-EPI (Chronic Kidney Disease Epidemiology Collaboration) [42] and the MDRD-IDMS (Modification of Diet in Renal Disease-Isotopic Dilution Mass Spectrometry) [43] equation and proteinuria were assessed by the albumin/creatinine ratio following the 2007 European Society of Hypertension/European Society of Cardiology Guidelines criteria [16]. Subclinical organ damage was defined as plasma creatinine between 1.3 - 1.5 mg/dl in men and 1.2 - 1.4 mg/dl in women, glomerular filtration rate below 60 ml/min or albumin/creatinine ratio > 22 mg/gr in men and 31 mg/gr in women. Renal disease was defined as plasma creatinine of 1.5 mg/dl or higher in men and 1.4 mg/l in women or albumin/creatinine ratio > 300 mg/24 h.

#### Evaluation of retinal involvement

Retinography was performed with a Topcon TRC NW 200 non-mydriatic retinal camera (Topcon Europe B.C. Capelle a/d IJssel The Netherlands), obtaining images centered on the papilla. Once the images were captured, two independent observers classified them according to the Keith-Wagener classification for hypertensive retinopathy [44], with a third reading being performed in cases where there were discrepancies. Grades III or IV (hemorrhages or exudates, papillary edema) are considered to be associated with cardiovascular disease [16].

#### Evaluation of pulse wave velocity and central blood pressure

The pulse wave velocity (PWV) was calculated using the SphygmoCor System (Vx Pulse Wave Velocity), (AtCor Medical Pty Ltd Head Office, West Ryde, Australia) with the patient in the supine decubitus position. The carotid and femoral pulse wave was analyzed, estimating the delay in the electrocardiograma (ECG) wave and calculating the PWV. The space measurements were taken with a measuring tape from the suprasternal notch to the carotid and femoral arteries at the sensor location. A measurement of greater than 12 m/s is considered subclinical organ damage [16].

Using the SphygmoCor system (Px Pulse Wave Analysis)(Atcor Medical, Australia), with the patient in the sitting position and resting the arm on a rigid surface, pulse wave analysis will be made with a sensor in the radial artery - using mathematical transformation to estimate the aortic pulse wave. From the aortic wave morphology, central (aortic) arterial pressure will be estimated, along with central ventricular load, diastolic perfusion pressure, the subendocardial viability index, the pressure increment, central pulse pressure and the augmentation index (PWA), defined as the percentage increase in central pulse pressure: AIx = pressure increase/pulse pressure * 100 [33].

All explorations will be carried out on a yearly basis, and due registry will be made of any changes in the sociodemographic variables or cardiovascular risk factors, and of the appearance of events.

### Organization of data collection

The patients referred to the research unit of La Alamedilla primary care center will be interviewed by a contracted nurse specifically trained for the project. A history will be compiled and a basic exploration will be carried out. A 24-hour ambulatory blood pressure monitoring (ABPM) device will be fitted, and the patients will receive an OMRON M7 sphygmomanometer for self-measurement of blood pressure at home. Vascular exploration will be made (pulse analysis with the SphygmoCor system, ABI and ECG), and an appointment will be made for blood sampling. Posteriorly, carotid artery ultrasound will be performed by two specifically trained members of the research team. Data input will be made using the Teleform system (Autonomy Cardiff Vista, California, USA), with a questionnaire previously designed for the project, and exporting the data to the SPSS version 15.0 statistical package (SPSS Inc., Chicago, Illinois, USA) for posterior analysis.

### Statistics analysis

A first descriptive analysis will be made of the sociodemographic and clinical characteristics of the study groups. The data will be presented with the mean and 95% confidence interval in the case of quantitative variables, and as frequency distributions for qualitative variables. The Pearson chi-squared test will be used to analyze associations between qualitative variables. The Student t-test for independent samples will be used to compare the means for the two arterial pressure groups. In turn, the analysis of repeated measures will be based on the McNemar test for qualitative data and the Student t-test for paired data in application to quantitative data.

Survival will be analyzed with the Kaplan-Meier and actuarial methods on each visit and at the end of follow-up. The log-rank test will be used for comparing survival in the two groups. Lastly, a Cox regression model will be developed to estimate the event risk between the groups, adjusting for the possible confounding variables analyzed in the study.

Hypothesis contrasting will establish an alpha risk factor of 0.05 as the limit of statistical significance. The SPSS/PC+ version 15.0 statistical package will be used (SPSS Inc., Chicago, Illinois, USA).

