### The following objectives have been established

To evaluate the prognostic value of central arterial pressure and pulse wave velocity in relation to the incidence and outcome of renal (microalbuminuria, diminished glomerular filtration and the appearance of terminal renal failure), cardiac (LVH) and vascular damage (IMT and ABI), retinal vascular impairment, and the appearance of cardiovascular episodes (cardiovascular mortality, ischemic heart disease and stroke) in patients with DM2.

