### Study subjects

Consecutive inclusion will be made of the patients referred to the research unit and who meet the corresponding inclusion criteria, i.e., patients diagnosed with DM2 and aged 20-80 years, with none of the following exclusion criteria: patients unable to comply with the protocol requirements (psychological and/or cognitive disorders, failure to cooperate, educational limitations and problems for understanding written language, failure to sign the informed consent document), patients participating or who will participate in a clinical trial during the study, and patients with serious comorbidities representing a threat to life over the subsequent 12 months.

The sample size has been calculated to determine the time the patients take in suffering an event - the latter being interpreted as morbidity-mortality or the appearance of new target organ damage. To this effect, two groups will be considered, classified according to the median central arterial pressure value. The study accepts an alpha risk of 0.05 and a beta risk of 0.30 in two-sided contrasting for the detection of a minimum difference in relative risk between the two groups of ≥ 2.5 points, and considering an events rate within the high central arterial pressure group (values above the median) of 35% at the end of the study period. A total of 52 patients are required in each group, estimating a loss to follow-up of 10%. A final total of 110 patients therefore will be included.

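### The tests named for the repeated measures contain no exposure term, so they cannot show whether organ-damage markers progress differently with central pressure or pulse wave velocity

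*Protocol article*

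**What the plan says.** The objectives section of the Protocol article begins "To evaluate the prognostic value of central arterial pressure and pulse wave velocity in relation to the incidence and outcome of renal" and goes on to cardiac, vascular and retinal damage and cardiovascular episodes. The Background and the abstract's Discussion describe the same aim as the evolution of the markers, and the main Discussion promises an account of their course over time. Two exposures are named side by side: central arterial pressure and PWV.

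The Study design section plans at least five visits, at baseline and then annually. On the markers, the measurement section says "All explorations will be carried out on a yearly basis".

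For the resulting series, the Statistics analysis section gives one method: "the analysis of repeated measures will be based on the McNemar test for qualitative data and the Student t-test for paired data". The same section also lists:
- a chi-squared test for qualitative variables;
- an independent-samples t-test of means between the two pressure groups;
- Kaplan-Meier and actuarial survival estimates with a log-rank test;
- a Cox model adjusted for possible confounders.

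The only groups that the article defines are in Study subjects: "two groups will be considered, classified according to the median central arterial pressure value".

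**The concern.** The objective is relational. It asks whether patients with higher central pressure or higher PWV have a worse course of intima-media thickness (IMT), ankle-brachial index (ABI), estimated glomerular filtration rate (eGFR), albumin/creatinine ratio, ECG or retinal findings. McNemar's test and the paired t-test ask whether one group of patients differs between two visits, and the exposure does not enter either.

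If the plan is followed as written, the yearly marker data will show whether the cohort changed. They will not show how that change relates to the exposures the study was set up to evaluate. A clear change over time could then be read as evidence on prognostic value when it is not.

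**Working it through.** **Step 1. Match each stated analysis to the objective.**

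| Stated analysis | Contains central pressure? | Contains PWV as exposure? | Addresses change in a marker? |
|---|---|---|---|
| McNemar, paired t-test | No | No | Yes, two visits at a time |
| Independent t-test of means | Yes, two groups | No | Not stated to be applied to change |
| Chi-squared | Not stated | Not stated | Not stated |
| Log-rank, Cox | Yes, two groups | No | Only first appearance of new damage, as part of the event |

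No row combines an exposure with progression or regression of a marker, and PWV appears as an exposure in none.

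**Step 2. What the sample size was built for.** Inputs from Study subjects:
- two-sided alpha 0.05 and beta 0.30;
- "minimum difference in relative risk between the two groups of ≥ 2.5 points";
- "an events rate within the high central arterial pressure group (values above the median) of 35% at the end of the study period".

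The low-group rate is 0.35/2.5 = 0.14, and the mean rate is 0.245. The two-proportion formula with pooled variance under the null gives

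n = [1.960 × √(2 × 0.245 × 0.755) + 0.524 × √(0.35 × 0.65 + 0.14 × 0.86)]² / 0.21² = (1.192 + 0.309)² / 0.0441 ≈ 51.1, so 52 per group.

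This matches the stated 52. The figure sizes a comparison of event rates and not a repeated-measures analysis.

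**Step 3. What the paired test responds to.** The article gives no SD of change for any marker, so SD = 1 is assumed and effects are in SD units. With 52 per group (104 in all):
- The pooled paired t-test depends on the average change. For changes of 0.5 and 0.5, or of 0.25 and 0.75, that average is 0.5, and 0.5 × √104 = 5.1 standard errors in both cases (slightly less in the second, because the spread between groups adds to the SD). For -0.3 and +0.3 the average is 0.
- A between-group test of change depends on the difference: 0.5/√(2/52) = 2.5 standard errors, and 0.6/√(2/52) = 3.1.

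Simulated rejection rates (20,000 runs, 52 per group):

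| True mean change, low / high group | Pooled paired t-test | Between-group test of change |
|---|---|---|
| 0.5 / 0.5 | 99.9% | 4.8% |
| 0.25 / 0.75 | 99.9% | 71% |
| -0.3 / +0.3 | 4% | 86% |

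The paired test gives the same answer in the first two rows, where the exposure effect is absent and present. It misses the third row entirely.

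**Step 4. Paired tests run separately in each group.** With the same true change of 0.29 SD in both groups, each paired test has roughly even odds of significance (0.29 × √52 = 2.1 standard errors). One group is then significant and the other is not in about 50% of runs, although nothing differs between them. The direct comparison rejects in 5%.

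**Step 5. What a direct comparison could detect.** At 70% power the detectable difference in change is (1.960 + 0.524) × √(2/52) = 0.49 SD with 52 per group. With 47 per group it is 0.51 SD.

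**Step 6. Use of all visits.** Suppose five equally spaced visits and independent within-patient errors with variance σ². The slope variance is 2σ²/16 = 0.125σ² from the first and last visits, and σ²/10 = 0.100σ² from all five, which is 20% less. If patients truly differ in slope, the gain shrinks. An assumed between-patient slope variance of 0.1σ² gives 0.225σ² against 0.200σ² (11% less), and 0.3σ² gives 0.425σ² against 0.400σ² (6% less).

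**The case against.** The strongest reply is that organ damage is already linked to exposure. Study subjects counts newly appearing organ damage as an event, and the Statistics analysis section compares central-pressure groups on that event by log-rank and adjusted Cox. This stands. A reader might infer from the choice of paired tests that nothing in the plan ties exposure to organ damage, and the article does not support that. Incidence by central-pressure group is covered. However, a time-to-event analysis does not measure how far IMT, eGFR or albumin/creatinine ratio moved, or whether existing damage regressed. The groups are also defined by central pressure only. PWV could at most enter the Cox model as one of the adjusting variables.

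Second, the independent t-test and the chi-squared test are not restricted to baseline and could be applied to change. That is possible, but the article does not say so. Such tests would be unadjusted, and the t-test is tied to the pressure groups.

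Third, this is a condensed article, and an analysis plan may exist. Model details, missing visits and multiplicity may properly be left to it, and none of these is raised as a fault here. The point concerns a method that the article does name and that does not fit its objective.

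Fourth, the article says the analysis will draw on a multicentre study of 800 patients. That addresses the number of end events. More patients do not put an exposure term into a paired test.

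A reader might also infer that all 10 visit pairs per marker will be tested. The article does not say which pairs will be compared, so no multiplicity charge follows.

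**Conclusion.** The point holds for progression and regression of the markers, and for PWV throughout. It does not extend to incident organ damage by central-pressure group, which has an adjusted analysis.

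The main defect is structural: the tests named for the yearly data do not contain the exposure. The comparison of what each test estimates shows this without any numerical assumption. The simulated rates illustrate its size and rest on an assumed SD of change of 1, normally distributed changes and 52 patients per group. The efficiency gain from using all visits is secondary. It is 20% at most under independent errors, and less if patients differ in slope.

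It would go too far to say that marker evolution is the only thing this sample can estimate. The sample was sized on a composite event that includes new organ damage, and the article gives no separate rate for clinical cardiovascular events.

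**What to change.** For each continuous marker (IMT, ABI, eGFR, albumin/creatinine ratio, Cornell product), analyse all yearly values with a linear mixed model. Give it a patient random intercept and slope, with terms for time, baseline exposure and exposure × time, and adjust for the same confounders as the Cox model. For binary damage, use GEE or mixed logistic models with the same terms. Fit these for central arterial pressure and separately for PWV. Name the exposure × time coefficient as the reported result for evolution, and keep the McNemar and paired t-tests as descriptive.

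A between-group comparison of change, or an analysis of covariance on the final value, would also bring in the exposure, but would use fewer of the visits.

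The cost is revised wording in the Statistics analysis section and a little more analysis work. No new data or visits are needed.
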